### Research Team

The research team will consisted of research manager, data manager, one communication officer, two field supervisors, two data editors, one echo technologist and the 10 data collectors in pairs (five males and five females) will be assigned for data collection.

### Training of Field team

The team will be rigorously trained over a six-week period in study techniques, including performing standardized BP and anthropometric assessments (For details, please refer Appendix for Training Manual). The accuracy and appropriateness of the study methods will be tested on the role models. Intra and inter observer reliability will be assessed by comparing repeat measurements performed on the same individual at different times by the same observer, and the same individual at the same time by the team of observers.

### Pre-testing

The objectives of pre-testing are to be sure that the:

- Interviewer are comfortable with the questionnaires
- Patients understand the questionnaire
- Questionnaire is appropriate according to the objectives of the study
- All the BP monitors works properly
- Data-entry program is compatible with the questionnaire

On completion of training, research team will go in the field to pre-test questionnaire. It will be done in about 10% of the sample size. The subjects, who would be selected for pre-testing, would not be the part of pilot study.

The entire process of pre-testing will be thoroughly observed by a group of observers including research manager for quality assurance. At the end of pre-testing all shortcomings including need of retraining of interviewers in some areas, revision of questionnaire and management problems in logistics will be addressed appropriately.

### Data Collection

The field team will pay home visits for inviting all enrolled subjects to participate in the study. Informed consent will be obtained. Reasons for not wishing to participate will be recorded. The subjects whose houses will be locked or those who will be out of city will be visited up to three times by the field team and thereafter, they will be labelled as not located. The data collection will be started from April 01, 2012 and anticipated to be completed by March 30, 2013. Following tools will be used for data collection:

*Questionnaires:*

The questionnaires are designed to be interviewer administered, prepared in English, All questionnaires will be translated in to Urdu and back translated and verified before starting the study. Following questionnaires will be used in the study

Form A (For individuals 40 years and above)

Form B (For individuals 15 – 39 years)

Form C (For children 11 – 14 years)

Cardiovascular Morbidity / Mortality questionnaire (For high risk group)

Verbal Autopsy (For high risk group)

Blood Pressure Measurements:

The precise measurement of BP is essential for valid comparisons to be drawn. Therefore a strict routine for BP measurement will be followed.In this study calibrated automated “OMRON Blood Pressure Monitors will be used for measuring BP of the study subjects. Blood pressure will be measured in the sitting position from the right arm after 5 minutes of rest using an appropriate sized cuff. The selection of appropriate size of cuff will based on the mid arm circumference (mid-point between the shoulder and elbow). It will be measured by measuring tape. There are three types of cuffs available for different mid arm circumferences:

Small cuffs: for individuals with arm circumference 17 – 22 cm

Large cuff: for individuals with arm circumference 22 – 32 cm

Extra large cuff: for individuals with arm circumference 32 – 42 cm

Three consecutive readings with an interval of about 05 minutes will be taken on the day prior to initiation of dietary intervention and the mean of the final two blood pressure readings will be used in the analysis as baseline blood pressure.

For the outcome assessment during study period, three consecutive readings of blood pressure with an interval of 05 minutes will be taken at each visit, and the mean of the final two readings on the last day of each intervention week will be used in the analysis.

Anthropometric Measurements

Height will be measured in centimetres with a height scale placed vertically to the hard flat wall with base at the floor level. Subjects will be advised to stand bare footed, looking straight with their back to the height scale, feet together and with their arms hanging loosely by their side.

Body weight will be measured in kilograms (0.1 kg accuracy) by using calibrated “Tanita Solar Powered Digital Scale 1631”. The scale will be placed on to a flat, hard surface directly exposed to room light. Subjects will be asked to remove their shoes, heavy outer garments like Jacket, coat, etc. and stand on the scale with evenly distributed weight on both feet.

Echocardiography:

The echocardiography of all hypertensive patients will be performed at field site by a trained technologist.

## Data Management

The Data will be collected in the 2nd half of the day and will be supervised in the field by spot checking of the filled questionnaires by supervisor. After data collection, the questionnaires will be reviewed next day in the morning by the data collectors and self-edited. If there are any discrepancies found then the questionnaire will take to the field on next day by the same data collector, and will be corrected. After collection, thorough scrutiny of all the completed questionnaires will be done at the CHS department of Aga Khan University by field supervisor and data editors. Coding of the data will be done by data editor with the preparation of codebook after discussion with data manager and research coordinator. The data manager or research coordinator would randomly check filled questionnaires before entry into the computers to ensure the data quality. Data will be double entered in EpiData 3.1 software by two different data entry operators and then be validated and corrected for any disparity by using Microsoft FoxPro/Access. After removing data entry discrepancies, the data will be exported to SPSS and SAS for analysis.

Finally, 10% of the questionnaires would be checked randomly to look for any error in data entry and for calculating the data entry error. If the error rate <0.3% then data would be considered clean. After random checking the frequencies will be run on data for logical error checking. If there are any logical errors found then the study subject will be contacted via phone or field visit to remove those errors. Thereafter, the clean data will be ready for further analysis.

# PLAN OF ANALYSIS:

- SAS version 9.13 will be used for analyses.A p value of <0.05 will be considered statistically significant. All analyses will account for clustering at the level of census by household, as this was also the unit of randomization.[62](#_ENREF_62)

## Primary & Secondary Outcomes:

For the main intention to treat analysis, the mean estimated value in each cluster for those with missing values at the final visit will be computed for all individuals with available measurements, and assigned to those with missing last follow-up measurements for individuals by cluster. This method of imputation of missing values has been shown to yield valid inferences and is recommended for large community intervention trials with small size clusters.[63](#_ENREF_63),[64](#_ENREF_64) The primary and secondary outcomes will be compared between randomised clusters using a nested mixed factorial design analysis of variance. Due to previously detected significant interaction between treatment assignments on BP in the high risk group, only four-way analysis will be performed in that group.[65](#_ENREF_65) A p value of <0.05 was considered to be statistically significant for the main effects. We will report the means and 95% confidence intervals for the treatment effects, adjusted for sex, age and baseline BP in the models. In addition, models will also be constructed after accounting for the baseline and post-trial measurement of fasting plasma glucose, and lipids (as indicated). In the model for CVD morbidity and mortality, albuminuria, LVMI, and E/E’ ratio we will also adjust for change in systolic BP from baseline to follow-up. The marginal adjusted probabilities will be used to calculate the risk ratios, and their 95% CI will be computed by the bootstrapping method.[66](#_ENREF_66)

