#### Morbid and Mortal Events

Information on cardiovascular morbid events requiring hospitalization were collected at 6 monthly intervals and adjudicated by cardiologists and neurologists masked to randomization status, using guidelines recommended by the American Heart Association.[21](#_ENREF_21) Data on mortality was tracked (explained below). Deaths due to myocardial infarction, coronary revascularization, heart failure or stroke were categorized as cardiovascular deaths. During 2 years of follow-up, there were 231 composite events (cardiovascular events leading to hospitalization or all-cause mortality), 212 deaths of which 95 were due to cardiovascular causes. While the study was not powered for hard outcomes, preliminary analyses revealed an age and sex adjusted hazard ratio (95% CI) for all cause mortality for HHE versus no HHE of 0.92 (0.59-1.43), and for trained GP versus usual care GP of 0.73 (0.47-1.14). No interaction was detected between HHE and GP training on either the composite outcomes or all-cause mortality.

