## Aims of the project

To determine the sustained impact of HHE and annual GP training, alone and in combination, at 7 years, including 5 years of post intervention follow-up on:

a) Primary

i) BP levels of all participants.

ii) Cardiovascular morbid events and all cause mortality in the high risk cohort.

b) Secondary

i) Behavioural risk factors including diet, physical activity, weight and tobacco use in all trial participants

ii) Clinical risk factors for CVD including plasma glucose and lipids, and albuminuria in the high risk cohort.

iii) Left ventricular (LV) mass index and diastolic dysfunction in the high risk cohort.

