## Hypotheses:

We hypothesize that at 6 years of follow-up:

- Children and young adults randomized to HHE versus no HHE will continue to have lesser rise in BP.
- Hypertensive adults randomized to HHE plus trained GP intervention will continue to have greater decline in BP than single or no intervention. They will also have experience greater decline in plasma glucose, serum cholesterol and urine albumin excretions levels, and have lower left ventricular mass index and less diastolic dysfunction.

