## Outcome Measures

*Primary:*

In all subjects:

- Change in systolic BP from baseline to mean of two post trial follow-up visits.
- Composite of CVD morbid events and all-cause mortality.

*Secondary:*

In all subjects:

- Change from baseline to post trial follow-up in the following: body mass index (BMI), waist hip ratio, current tobacco use, total physical activity, and dietary intake of fruit and vegetables.

In the high risk cohort

- Percent change in plasma glucose (and incident pre-diabetes or diabetes defined as (fasting plasma glucose 100 mg/dl (5.5mmol/L) or more or initiation of hypoglycaemic agent)[58](#_ENREF_58), total and LDL cholesterol (and incident hyperlipidemia defined as total serum cholesterol >=200 mg/dl (5.18 mmol/L); LDL cholesterol >=130 mg/dl (3.37mmol/L))[59](#_ENREF_59), albumin excretion rate (and incident albuminuria defined as spot urine albumin to creatinine ratio of 30mg/g or greater)[60](#_ENREF_60) , and estimated glomerular filtration rate from baseline to post trial follow-up;
- Left ventricular mass index and E/A’ ratio at post trial follow-up.[39](#_ENREF_39),[61](#_ENREF_61)

Ancillary:

In the high risk cohort

- Overall mean score on Patient Health Related Quality of Life (HRQOL) based on 36-Item Short-Form Survey.

Data Collection and Management

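### The models for the co-primary CVD/mortality composite, albuminuria, LVMI and E/E' adjust for change in systolic BP, a post-randomisation mediator, without an explanatory label or a named main model

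*Protocol*

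**What the plan says.** The composite is a primary outcome. Outcome Measures (2.4) lists "Composite of CVD morbid events and all-cause mortality" under Primary, and the Aims (1.4) make "Cardiovascular morbid events and all cause mortality in the high risk cohort" a primary target of the two interventions. The other primary outcome in 2.4 is the change in systolic BP between baseline and the average of two post-trial visits. The Hypotheses (1.5) add that the combined group will "have lower left ventricular mass index and less diastolic dysfunction".

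Section 3.1 of the Plan of Analysis then makes four statements in sequence:

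1. Treatment effects are reported with confidence intervals, "adjusted for sex, age and baseline BP in the models".
2. "In addition, models will also be constructed after accounting for the baseline and post-trial measurement of fasting plasma glucose, and lipids", where indicated.
3. In the model for CVD morbidity and mortality, albuminuria, LVMI and E/E', "we will also adjust for change in systolic BP from baseline to follow-up".
4. Risk ratios are derived from marginal adjusted probabilities, with bootstrap intervals. The model they come from is not named.

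Earlier in 3.1, participants with a missing final measurement are given their cluster's mean. No exception is stated for people who died.

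**The concern.** Change in SBP is affected by the interventions and is a main route by which they are meant to act. Section 1.3.1 gives the purpose of the follow-up as seeing whether BP is kept lower and whether this carries over into fewer cardiovascular events. A model that holds SBP change fixed asks what the interventions do apart from BP. That is a legitimate question, but it is not the sustained impact named in the Aims.

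The composite has a second problem, which is timing. Post-trial SBP is taken in 2012-13, after the events it would be used to explain. Those who died earlier have no such measurement, and those with an earlier non-fatal event have it measured after the event.

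At stake is which number answers a co-primary aim. As 3.1 is written, an analyst could take the risk ratio for the composite from either model and be following the protocol.

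**Working it through.** The protocol gives no effect size or power figure for these models, so there is no stated result to reproduce.

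**Step 1. BP difference available to be adjusted away.** From the in-trial table in 1.2.3 (adjusted decline in SBP at 2 years; groups of 332, 348, 335 and 326, total 1341, which agrees with the text):
- combined versus none: 10.8 − 5.8 = 5.0 mm Hg
- combined versus either single intervention: 10.8 − 5.6 = 5.2 mm Hg
- either single intervention versus none: 5.6 − 5.8 = −0.2 mm Hg

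The issue therefore bites on contrasts with the combined group. These are 2-year figures; the post-trial difference is not known.

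**Step 2. What adjustment does when SBP change is measured.** On the scale of the linear predictor, approximately:

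total effect = direct effect + b × (difference in SBP change)

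Adjusting for SBP change leaves the direct term, and even that holds only if no unmeasured factor drives both SBP change and the outcome. The fraction lost equals the share mediated by BP. This applies most directly to LVMI, E/E' and albuminuria, which are measured at the post-trial examination.

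**Step 3. Illustration on a binary outcome.** A logistic simulation compared combined with no intervention, using the 5.0 mm Hg difference and an SD of SBP change of 18 mm Hg. The SD comes from the published intervals: for the combined group, (12.8 − 8.9)/(2 × 1.96) × √332 = 18.1; the four groups give 17.5 to 18.1. Assumptions not in the protocol: 25% event risk, an odds ratio of 1.2 or 1.4 per 10 mm Hg, and 50 to 100% of the effect through SBP. There were 40 replicates of 6,700 subjects, with no between-cluster variance and Monte Carlo error of about 0.02.

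| Share through BP | OR per 10 mm Hg | OR without SBP change | OR with true SBP change |
|---|---|---|---|
| 100% | 1.2 | 0.93 | 1.02 |
| 100% | 1.4 | 0.86 | 1.01 |
| 75% | 1.2 | 0.89 | 0.97 |
| 75% | 1.4 | 0.82 | 0.96 |
| 50% | 1.2 | 0.84 | 0.92 |
| 50% | 1.4 | 0.72 | 0.84 |

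As a check on the last row, ln 0.72 = −0.33 and ln 0.84 = −0.17, so about half of the log odds ratio is lost.

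**Step 4. The composite, where SBP change is mostly unmeasured.** Section 1.2.3 reports that "there were 231 composite events (cardiovascular events leading to hospitalization or all-cause mortality), 212 deaths of which 95 were due to cardiovascular causes". Then 212/231 = 91.8%, leaving 231 − 212 = 19 composite events without a death. The simulation took 90% of events as fatal and tried two ways of handling the dead.

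- *Cluster mean given to the dead* (applied to the change score, a simplification of the rule in 3.1). At full mediation the OR moved from 0.91 to 0.92 (OR 1.2 per 10 mm Hg) and from 0.86 to 0.88 (OR 1.4). The true direct effect in both cases is an OR of 1.0. The result is therefore not the direct effect, and it is no longer a clean estimate of the total effect.
- *The dead dropped.* About 10% of events remain under the 90% assumption, or 19/231 = 8% on the 2-year counts.

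**The case against.** The strongest reply is that 3.1 already contains the right main model. It first reports treatment effects adjusted for age, sex and baseline BP, and only then turns to additional models, so the SBP-change model can be read as one more explanatory step. The protocol also has a reason to want such a model. Section 1.3.1 discusses trials in which BP and CVD effects came apart and mentions benefits beyond BP reduction, and 1.3.3 looks for clues to mechanism.

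Much of this stands. The documents do not support saying that the SBP-adjusted model is the primary one, and they give no ground for deleting explanatory models outright. The glucose and lipid models are expressly additional. What does not stand is that the text settles the matter. The SBP sentence speaks of the model for these outcomes, in the singular. The risk-ratio sentence follows it directly without naming a source. By contrast, 3.2 asks for quality-of-life results with and without adjustment for medication; no such pairing is given here.

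Three further inferences are tempting and go too far.
- *That adjustment wipes out the effect on the composite.* Only the BP-mediated part is at risk, and with cluster means given to the dead the estimate hardly moves.
- *That the covariate cannot exist for those who died.* No post-trial value is measured, but 1.3.5 describes 6-monthly in-trial readings in the high risk cohort, and the sentence in 3.1 does not define follow-up. Applying the imputation rule to this covariate is itself an inference.
- *That 92% of events will be deaths in the final analysis.* That is a 2-year figure whose denominator population is not stated.

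**Conclusion.** The point holds as one of estimand and model status. Section 3.1 puts a post-randomisation variable, itself a primary outcome and a hypothesised mediator, into the model for a co-primary outcome and three others, and does not say whether that model supplies the reported result.

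For LVMI, E/E' and albuminuria, adjustment removes the BP-mediated share of the effect. That share is unknown; an assumed 50 to 100% means a loss of the same proportion, and the 5 mm Hg behind it applies only to the combined group against the others at 2 years.

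For the composite, the fault is an estimate that cannot be interpreted, and large attenuation is not shown. Under cluster-mean imputation it is neither the total nor the direct effect; if the dead are dropped, most events go, provided later events resemble the first 2 years in being mainly deaths. The odds ratios above are illustrations under the stated assumptions and are not predictions for this cohort.

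**What to change.** Rewrite the adjustment sentences in 3.1 to say:

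- The main model for the composite, albuminuria, LVMI and E/E' contains treatment, sex, age and baseline BP, plus the baseline value of the outcome where it was collected, and accounts for clustering. Change in SBP is not in it.
- The reported risk ratios and their bootstrap intervals come from that model.
- Any model with SBP change, or with post-trial glucose or lipids, is an exploratory mediation analysis. For each, state which SBP reading defines follow-up, how people who died are handled, and how events that precede the covariate measurement are treated. One option for the composite is to use in-trial SBP up to 24 months and count only later events; for LVMI and E/E', the analysis would be confined to examined survivors.

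The cost is one paragraph of analysis text. No new data are needed, and the mechanistic question in 1.3.1 and 1.3.3 is kept.

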# METHODS

All participants in the trial (originally aged 5 and now 13 years or over) will be visited by trained field staff masked to randomization status. However, the individuals (children or individuals aged 15 – 39 years) not enrolled in the main study, pregnant women, bed ridden and/or mentally retarded study subjects unable to consent will be excluded. Eligibile subjects will be offered informed consent. The date and time for interview will be set at individual’s convenience after obtaining informed consent. Information on socioeconomic status assessed via household possessions and income, occupation and literacy status, diet, physical activity (modified IPAQ), and tobacco use would be collected and weight, height, waist and hip circumference would be measured. In addition, questionnaires on health related quality of life (SF-36 and EQ-5D) will be administered to all subjects aged 40 and over with hypertension after translation in Urdu and pre-testing. As collected during baseline, the names and doses of current anti-hypertensive medications will be recorded.

As during the COBRA trial, BP will be measured with a calibrated automated device, Omron HEM-737TM Intellisense BP Monitor, in the sitting position after 5 minutes of rest using an appropriate sized paediatric or adult cuff, as applicable.[51](#_ENREF_51) BP measurements will be repeated after two weeks. Three consecutive readings will be taken at each visit, and the mean of the final two used in the analysis. The visits will be balanced across the four randomised groups and planned during the first half of the day to minimise seasonal and diurnal variation in measurements, respectively. Maximum three visits will be paid for those not present at a scheduled date and thereafter, they will be labelled as lost to follow-up.

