## Assessment of morbid and mortal events:

As during the main trial, all subjects aged 40 years and above in the cohort will be tracked for assessment of morbid CVD events requiring hospitalizations or death during the entire 6 years of follow-up. Since data from the initial 2 years were collected at 6 monthly intervals, relevant information during the last 4 years will be extracted from district-level official mortality registers in each cluster to track mortality. A standardized questionnaire on mortality or hospital admission during the last four years will be administered in a culturally sensitive fashion. In cases of death, the cause of death reported by the nearest family member will be recorded, and the WHO verbal autopsy questionnaire will be administered. Complete death records will be extracted, where available. However, some degree of uncertainty is expected with ascertainment of cause of death is expected in capturing mortality data on verbal autopsy from beyond the last one year. All those who report admission to hospital for a cardiovascular event, or a stroke like event will be subsequently evaluated by a study cardiologist or neurologist to confirm the diagnosis per recommendations of the American Heart Association and the European Society of Cardiology.[21](#_ENREF_21) On ethical grounds, all these patients will also be given advice regarding treatment for any complications, and prevention of future events.

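### The co-primary composite is given a risk ratio with no follow-up time, although after year 2 non-fatal admissions are seen only for people or families who are re-contacted

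*Protocol*

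**What the plan says.** Outcome Measures lists as co-primary: "Composite of CVD morbid events and all-cause mortality".

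Primary & Secondary Outcomes fixes the method: "The primary and secondary outcomes will be compared between randomised clusters using a nested mixed factorial design analysis of variance". The effects are adjusted for sex, age and baseline BP. For cardiovascular morbidity and mortality the section adds: "we will also adjust for change in systolic BP from baseline to follow-up". The next sentence is: "The marginal adjusted probabilities will be used to calculate the risk ratios, and their 95% CI will be computed by the bootstrapping method". Missing final values get a cluster mean, which is "assigned to those with missing last follow-up measurements for individuals by cluster".

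The window is described as common to all. Assessment of morbid and mortal events says subjects aged 40 and above will be "tracked for assessment of morbid CVD events requiring hospitalizations or death during the entire 6 years of follow-up". Aims of the project gives 7 years, 5 of them after the intervention.

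The same assessment section describes ascertainment after year 2. Deaths are sought from the district-level registers in each cluster, from the nearest relative and by verbal autopsy. Admissions come from a questionnaire covering the last four years. Methods adds: "Maximum three visits will be paid for those not present at a scheduled date and thereafter, they will be labelled as lost to follow-up".

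The in-trial mortality result was a time-to-event estimate: "age and sex adjusted hazard ratio (95% CI) for all cause mortality for HHE versus no HHE of 0.92 (0.59-1.43".

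**The concern.** A proportion with an event over a fixed window means the same thing in each arm only if everyone is observed for that window, or if the analysis accounts for those who are not. Here a person last seen at one year and a person interviewed in 2012 or 2013 enter on equal terms.

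For admissions, the first person's later experience is simply unseen. If such people count as event-free, absolute risks are too low, and the ratio shifts wherever loss differs by arm. If they are dropped, their observed event-free time is lost. If they receive a cluster mean, observed time is still ignored.

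With 12 clusters over four groups, about three per group, a chance imbalance in loss is plausible. The result also could not be set beside the hazard ratios for years 0 to 2.

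**Working it through.** The protocol gives no sample size, power or event target for the composite, so there is no design figure to reproduce. The four arms do add up: 332 + 348 + 335 + 326 = 1,341.

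**How many people could have short observation of admissions**
- High risk cohort (Main Trial findings): follow-up data on 78% of 1,341, so 0.22 × 1,341 ≈ 295 without.
- Methods: about 15% of those lost are expected back. Remaining: 0.22 × 0.85 = 18.7%, or about 251 people.
- If the 15% meant percentage points: 0.22 − 0.15 = 7%, or about 94 people.
- The 22% may include people who died, so 18.7% is an upper bound for unknown event status.

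**How much observed time differs.** In-trial contact was 6-monthly. Someone last seen at 2, 1 or 0.5 years, set against 6 years, has 6/2 = 3, 6/1 = 6 or 6/0.5 = 12 times less time. Against 7 years the factors are 3.5, 7 and 14. These follow from the schedule; the protocol gives no individual times. Among those located, visits run from April 2012 to March 2013, so follow-up can also vary by up to a year.

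**How much of the composite is exposed.** Morbid and Mortal Events gives 231 composite events and 212 deaths in 2 years. 212/231 = 92%, leaving 231 − 212 = 19 non-fatal events if each person counts once. Most of the composite is the component that the registers are meant to capture.

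**Effect on the risk and the ratio.** Assumptions: constant hazard, loss at about 1 year, and people not found counted as event-free apart from a share c of later events that is still captured. The denominator for the 231 events is not stated, so two are used: 1,341 (high-risk cohort) and 3,143 (all aged 40 and over).

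- Hazard: λ = −ln(1 − 231/N)/2, which is 0.0945 or 0.0382 per year.
- True risk: R(t) = 1 − exp(−λt), so R(6) = 43.3% or 20.5%.
- Apparent risk: (1 − L)·R(6) + L·[R(1) + c·(R(6) − R(1))], with L the proportion lost.

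Equal loss (L = 18.7% in both arms, c = 0): the apparent 6-year risk is 36.9% instead of 43.3%, or 17.3% instead of 20.5%. The ratio stays at 1.00 under no effect. With a hazard ratio of 0.73 and N = 1,341 it moves from 0.783 to 0.781, a change of 0.3%.

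Unequal loss (13.7% versus 23.7%, an assumed 10-point difference in either direction), true ratio 1.00:

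| Later events captured (c) | N = 1,341 | N = 3,143 |
| --- | --- | --- |
| 0 | 1.097 or 0.911 | 1.101 or 0.908 |
| 0.5 | 1.044 or 0.958 | 1.045 or 0.957 |
| 0.92 | 1.006 or 0.994 | 1.007 or 0.993 |

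The last row roughly represents capture of all later deaths and no later admissions, if the in-trial mix persists.

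**Whether the window itself is defined.** The event section says 6 years and the aims say 7. Data collection in the main trial ended by December 2007. A four-year look-back from visits in April 2012 to March 2013 begins between April 2008 and March 2009, so it does not join up with the in-trial period.

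**The case against.** A reader might infer that all events are invisible after last contact. The protocol does not support that. Registers, relatives, verbal autopsy and a dedicated tracing team do not depend on the participant's own contact, and deaths made up most of the in-trial composite. The gap concerns mainly admissions, and also people who left the area of a cluster's register; the background section itself acknowledges limits of vital registration.

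A reader might also infer that people not found will be counted as event-free, or that the ratio is materially biased. Neither is stated or shown. The only missing-value rule in the text is the cluster mean, which would give lost people their cluster's event proportion. No figure shows differential loss by arm. Methods also balances visits across the four groups. That is aimed at seasonal variation, but it limits differences in follow-up length by arm among those located. These points stand, and they are why the effect on the ratio is given only as a conditional range.

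It can further be said that the risk-ratio sentence does not name the composite, that marginal probabilities could come from a survival model, and that censoring details belong in an analysis plan that is not at hand. This stands only in part. The sentence directly follows the one on the morbidity and mortality model, and the composite is the only co-primary outcome to which a risk ratio can apply. If the sentence covered secondary outcomes alone, the composite would be left with analysis of variance, which ignores time too. A method is stated here, and it departs from the trial's own in-trial hazard ratios.

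Finally, censoring unlocated people at their last in-trial contact would leave some known deaths out of the composite and could make censoring informative. That is a fair criticism, and the fix must deal with it openly.

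**Conclusion.** The concern holds in a limited form. The stated analysis of the co-primary composite has no follow-up time and presumes a common window that the protocol gives as both 6 and 7 years. After year 2, observation of non-fatal admissions depends on re-contact. Between about 7% and 19% of the high-risk cohort, depending on how the recapture figure is read, may have only in-trial observation of that component, with 19% an upper bound.

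The ratio is robust if loss is equal across arms (change of at most about 0.3%). Absolute risks are understated if people not found count as event-free, which the protocol does not say. A distortion of about 10% in the ratio needs both an assumed 10-point difference in loss and no later capture. It shrinks to about 4% with half of later events captured, and below 1% with 92% captured. The extreme case is about as far from 1 as the in-trial HHE estimate of 0.92.

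All of these ratio figures rest on a constant hazard, loss at about one year and the assumed loss pattern. The case for change is that a better-defined analysis is available at little cost, not that bias has been demonstrated.

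**What to change.** - Analyse the composite as time to first event (Cox, or Poisson with person-time), with inference that respects the 12 clusters.
- Censor each person at the last date on which both components could be ascertained: the post-trial visit or proxy interview, otherwise the last in-trial contact.
- Do not apply cluster-mean imputation to this outcome.
- Report person-years by arm. If a risk ratio is wanted, take it at a fixed time from the same model.
- Analyse all-cause mortality, including register-only deaths, with its own censoring date. Add a sensitivity analysis that counts register-only deaths in the composite.
- Reconcile the 6-year and 7-year windows.
- Record the month of each reported admission on the planned questionnaire.

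The cost is analysis wording plus one questionnaire item. In-trial contact was 6-monthly and mortality was analysed by hazard ratio, so event times for that period should exist. The drawbacks are that admission dates recalled over four years are approximate, and that the analysis assumes non-informative censoring.
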